#### **9.2.5 Relationship**

The relationship or association of the study medication in causing or contributing to the AE will be characterized by the Investigator using the following classification and criteria:

- Possibly or probably related: A clinical event, including laboratory test abnormality, with a reasonable time sequence to study medication administration that might or might not be also explained by concurrent disease or other drugs or chemicals.
- Not related: A clinical event, including laboratory test abnormality, judged to be clearly and incontrovertibly due to extraneous causes (e.g., diseases, environment), or with a temporal relationship to study medication administration that makes a causal relationship improbable, and/or for which other drugs, chemicals, or underlying diseases provide a much more plausible explanation.

If applicable, the relationship of the AE to the study medication will be assessed by means of the question: "Is there a reasonable possibility that the event may have been caused by the investigational product?" The Investigator should respond to this question with either "Yes" or "No" separately for each study medication.

### **9.2.6 Severity**

Severity or intensity will be assessed according to the NCI CTCAE v5.0 severity grading scale.

Grade refers to the severity of the AE. The NCI CTCAE v5.0 displays Grades 1 through 5 with unique clinical descriptions of severity for each AE based on this general guideline:

- Grade 1: Mild (awareness of sign or symptom, but easily tolerated)
- Grade 2: Moderate (discomfort sufficient to cause interference with normal activities)
- Grade 3: Severe (incapacitating, with inability to perform normal activities)
- Grade 4: Life-threatening (urgent intervention indicated)
- Grade 5: Death related to AE.

### **9.3 Follow-up of adverse events**

All AEs will be followed until they have abated, or until a stable situation has been reached.

Depending on the event, follow up may require additional tests or medical procedures as indicated, and/or referral to the general physician or a medical specialist.

SAEs need to be reported till end of study within the Netherlands, as defined in the protocol.

### **9.4 [Data Safety Monitoring Board (DSMB) / Safety Committee]**

An independent DSMB is installed, comprising chair: [name] gastroenterologist-hepatologist at Leiden UMC, [name], emeritus professor of internal medicine at Amsterdam UMC, location AMC and [name], statistician and epidemiologist at Amsterdam UMC, location AMC before the trial will be initiated. All members of the DSMB do not have a conflict of interest concerning this study.

The main focus of the DSMB will be safety of the participants and compliance to the study protocol (see also the enclosed DSMB charter).

The advice(s) of the DSMB will be sent to the sponsor of the study and the chief medical officers of A-Mansia Biotech and Caelus Health. Should the sponsor of the study decide not to fully implement the advice of the DSMB, the sponsor will send the advice to the reviewing METC, including a note to substantiate why (part of) the advice of the DSMB will not be followed.

## 10. STATISTICAL ANALYSIS

Statistical analyses will be performed by SPSS statistical analysis software and R-studio.

Normality of the data will be assessed by a Kolmogorov–Smirnov test. Data transformation will be done if the data is not normally distributed. The primary analyses of studied primary parameters will be performed between the baseline and endpoint intervention by analysis of a two-tailed one-sample t-test, or chi-square test. If the data is not normally distributed and data transformation is not possible, the Mann-Whitney test will be used. Further associations will be assessed with Pearson rank correlation test / Pearson chi-square test.

Paired categorical data will be analyzed with McNemars test. Paired continuous data will be analyzed using a paired T-test when normally distributed, and a Wilcoxon signed-rank test when not normally distributed.

Using R, we will use statistical packages that employ machine-learning algorithms to reveal which metabolites and microbiota best predict favourable response. An Elastic Net machine learning classification algorithm in combination with a stability selection procedure will be used to identify biological features that change differently between the two treatment groups. Also using R, a deep-learned algorithm scoring whole slide images of liver biopsies will be applied and analyzed.

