Throughout the study period, the participants will, in addition to the LFMT or placebo capsules, take the 3 bacterial strains in the morning combined with FOS. They will further be asked to retain their usual dietary habits during the study and to keep a nutritional diary from week -1 to 24 to monitor caloric intake including total calories, dietary carbohydrates, fat, proteins, and fibers. Blood pressure, body weight, and changes in health status will be documented.

Interventions: From the day of the first LFMT capsules until completion of the study, all participants will receive an oral daily dose of 5 grams of fructo-oligosaccharides [Sensus, Roosendaal]. Subsequently, participants will be randomized to receive lean donor LFMT or placebo capsules. This consists of 21 capsules at the first 3 study visits, and a daily ingestion of 2 capsules during the duration of the study (24 weeks). Placebo capsules will consist of saline with a brown pigment. During the 24 week study duration, all participants will also daily take  $10^9$  *A. soehngenii* CH-106 cells (dosage based on previous studies and safety study; provided by Caelus Health),  $10^{10}$  *B. animalis* subsp. *lactis* BLC1 (commercially available Sacco SRL) and  $3 \times 10^{10}$  pasteurized *A. muciniphila* cells (provided by A-Mansia Biotech), and 5 grams of FOS. We have previously observed that gut microbiota composition in the recipient is affected up to 8-12 weeks after donor FMT, so this time window ensures a stable donor gut microbiota composition during the study. The fecal donor samples will be collected, lyophilized ('freeze-dried'), encapsulated and stored at -80°C (see also paragraph 6.8). At home, participants will store the LFMT capsules in the freezer (-20°C). See figure 6 below.

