#### 8.1.3 Secondary outcomes

##### Secondary outcomes

To demonstrate that the combined treatment improves:

- non-invasive outcomes of NAFLD, i.e. multiparametric MRI of liver and surrounding subcutaneous adipose tissue (MRI-PDFF, MR elastography, corrected T1), FibroScan Elastography and Controlled Attenuation Parameters, and plasma panel Enhanced Liver Fibrosis (ELF) panel, pro-C3.
- change in blood markers from baseline to end of treatment, namely: liver enzymes (i.e. alanine amino transferase (ALT), aspartate amino transferase (AST), gamma glutamyl transferase (GGT), alkaline phosphatase (ALP)), inflammatory blood markers (i.e. leukocytes, monocytes, CRP, IL-1( $\beta$ ), IL-6, IL-11, IL-17, IL-32, TNF- $\alpha$ , IFN- $\gamma$ , additional markers of inflammatory pathways), SCFA (i.e. propionate, butyrate, acetate), lactate, ethanol, plasma lipids (i.e. LDL, HDL, triglycerides, total cholesterol), FGF-21, adiponectin, leptin, lipopolysaccharides, zonulin, estrogen, vitamin B12, folate acid, other metabolomic and lipodomic outcomes.
- microbiome read outs (composition, engraftment, strain tracking) en metabolites, fecal SCFA-composition, and fecal albumine
- glycemic control, insulin resistance, body weight/BMI, waist circumference and percentage body fat
- MetSy criteria / %
- SCFA production and GLP1 gene and protein expression indicating GLP-1 production
- liver gene expression profile: lipogenic, inflammatory and fibrogenic pathways
- liver pathology, histopathological features, immunofluorescence and assessment of pathophysiological proteins

- NAFLD histology as assessed with a deep-learned algorithm scoring whole slide images of liver biopsies.
- 
- Continuous glucose monitoring (4x 7 consecutive days)
- quality of life (general (SF36) and NAFLD/NASH-specific (CDLQ-NAFLD)).

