#### *Fecal samples*

In addition, feces will be collected at baseline, and after 2, 8, 10, 16, 18 and 24 weeks for extensive microbiota analysis and intestinal barrier function assessment.

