#### *Blood withdrawal*

Blood will be collected at baseline, 8, 16 and 24 weeks. At baseline and 24 weeks, blood will be investigated on common liver enzymes, indicators of glycemic control, lipids, and general and more NASH-specific parameters. Blood withdrawal on 8 and 16 week is for safety and in a lesser extent for study purposes (e.g. enhanced liver fibrosis-panel).

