#### *Food diary, glucose monitoring and questionnaires*

Participants will, moreover, keep a diary of their daily food intake for 5 days in the week before and after study visits. In addition, they will fill in questionnaires physical endurance and quality of life at baseline and 24 weeks.

Last, continuous glucose measurements will be performed at house using portable devices, during a consecutive period of 1 week (7 days) in the week before baseline, week 1, 9, 17 and 25.

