### *Blood withdrawal*

Last, blood withdrawal, which happens 5 times, can be unpleasant, and can cause self-limiting (sub)cutaneous hemorrhage/bruising.

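### Section 10 prescribes only two-time-point or two-group tests for continuous data, so it has no between-arm method for the stool and glucose outcomes measured five to seven times

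*Protocol*

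**What the plan says.** **Sampling.** Protocol section 8.3 (Fecal samples) states that "feces will be collected at baseline, and after 2, 8, 10, 16, 18 and 24 weeks for extensive microbiota analysis", which is seven times. Glucose is monitored for seven days "in the week before baseline, week 1, 9, 17 and 25" (section 8.3, Food diary, glucose monitoring and questionnaires), which is five weeks. For blood, section 8.3 says "Blood will be collected at baseline, 8, 16 and 24 weeks", and adds that "Blood withdrawal on 8 and 16 week is for safety and in a lesser extent for study purposes".

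**Outcomes.** Section 8.1.3 lists fecal SCFA, fecal albumin, microbiome read-outs and continuous glucose monitoring among the secondary outcomes. The blood outcome is defined there as "change in blood markers from baseline to end of treatment".

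**Analysis.** For paired continuous outcomes, section 10 says: "Paired continuous data will be analyzed using a paired T-test when normally distributed, and a Wilcoxon signed-rank test when not normally distributed". It also names a one-sample t-test, chi-square, Mann-Whitney, McNemar and correlation tests. An Elastic Net with stability selection is to find features whose change differs between the arms. No method for more than two time points per patient is named.

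**Counts that disagree.** The outcome list in section 8.1.3 and the glucose paragraph of section 11.3 give four glucose weeks, against five in section 8.3. Section 11.3 says "blood withdrawal, which happens 5 times, can be unpleasant", against four draws in section 8.3.

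**The concern.** Section 10 is not silent on continuous data. It assigns tests, and those tests do not fit the series that section 8.3 collects. A paired t-test or signed-rank test on a stool marker has three consequences:

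- It tests change within one arm. Both arms receive the synbiotic, so a within-arm change cannot isolate the LFMT effect, which is the randomised contrast.
- It uses two samples per patient. With baseline and week 24, the other five of seven stool samples do not enter.
- It needs both samples, so a patient without a week-24 sample contributes nothing, however many intermediate samples exist.

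These outcomes carry the mechanistic secondary objective in 48 patients, so an inefficient or non-randomised comparison is costly.

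**Working it through.** **The plan's own figure.** Section 4.4 gives 24 per arm at alpha 0.05 and power 0.80, for the primary outcome only. No SD, within-person correlation or power is given for any secondary outcome, so there is no secondary-outcome power to reproduce. I take n = 24 per arm and a two-sided 0.05 test. The other inputs are assumptions.

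**Assumptions.** Unit variance at each visit; equal within-person correlation ρ between visits, 0.5 with range 0.3-0.7; an LFMT effect of 0.5 SD, constant from the first post-baseline sample; complete data.

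**Variance per patient of each between-arm analysis:**
- change at week 24: 2(1 − ρ)
- week 24, baseline-adjusted: 1 − ρ²
- mean of m post-baseline values, baseline-adjusted: [1 + (m − 1)ρ]/m − ρ²

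Here m = 6 for stool and 4 for glucose. The noncentrality is 0.5/√(2v/24), with power from the noncentral t distribution (46 df, or 45 with a baseline covariate).

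**Worked at ρ = 0.5, stool:**
- change: v = 1.00, noncentrality 1.73, power 0.40
- adjusted week 24: v = 0.75, noncentrality 2.00, power 0.50
- adjusted mean of six: v = 3.5/6 − 0.25 = 0.333, noncentrality 3.00, power 0.84

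**Power over the range of ρ:**

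| Analysis | ρ = 0.3 | ρ = 0.5 | ρ = 0.7 |
|---|---|---|---|
| Change at last time point | 0.30 | 0.40 | 0.59 |
| Adjusted last time point | 0.43 | 0.50 | 0.66 |
| Adjusted mean, stool (m = 6) | 0.84 | 0.84 | 0.91 |
| Adjusted mean, glucose (m = 4) | 0.78 | 0.79 | 0.89 |

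Simulation with 20,000 trials per setting agrees within about 0.01 for the change and stool rows (for example 0.42 for adjusted week 24 and 0.83 for the stool mean, both at ρ = 0.3).

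**Where the gain comes from.** At ρ = 0.5, baseline adjustment moves power from 0.40 to 0.50, and averaging moves it from 0.50 to 0.84. With complete data, the week-24 contrast of a mixed model gains little or nothing from the intermediate visits. Most of the gain therefore belongs to the time-averaged contrast, not to the model as such.

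**If the effect builds up linearly to 0.5 SD at the last time point.** The mean post-baseline stool time is (2 + 8 + 10 + 16 + 18 + 24)/6 = 13 weeks, so the averaged effect is 13/24 × 0.5 = 0.27 SD. The power of the stool mean becomes 0.36, 0.36 and 0.44 at ρ = 0.3, 0.5 and 0.7, against 0.43, 0.50 and 0.66 for the adjusted week-24 comparison. For glucose the mean time is (1 + 9 + 17 + 25)/4 = 13 weeks, the averaged effect is 13/25 × 0.5 = 0.26 SD, and power is 0.30, 0.30 and 0.38. Averaging then loses against the adjusted last-visit comparison.

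**The case against.** **This belongs in the SAP.** Models for repeated secondary measures are often left there, and section 10 does not claim that its list is exhaustive. That would answer a silent protocol. This one names tests for paired continuous data, and those tests do not compare the arms or use a series, so the choice stated is a poor one.

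**The Elastic Net already covers the microbiome.** It does address between-arm change in features, and the text does not say which visits it uses. A reader therefore should not infer that the intermediate stool samples are wasted. It still yields no LFMT-placebo estimate for a named outcome such as fecal SCFA or albumin.

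**Mann-Whitney could be applied to a post-baseline mean.** It could, and the averaging gain does not require a mixed model. But section 10 offers that test as a fallback for non-normal data and pre-specifies no summary measure.

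**The averaged target is a preference.** The protocol's claim that the dosing schedule works "so this time window ensures a stable donor gut microbiota composition during the study" concerns donor composition. It makes a sustained effect plausible but does not establish a constant effect on SCFA, albumin or glucose. Samples two and eight weeks after each loading dose also suit a study of time course. This stands, and is why the last-visit contrast must be reported too.

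**Stronger readings the documents do not support:**
- *About half the power is lost.* At ρ = 0.5 under a constant effect, the stool shortfall is 1 − 0.40/0.84 = 52% against the change score, but 1 − 0.50/0.84 = 40% against the adjusted comparison. It varies with ρ and reverses if the effect builds late. The protocol supplies none of these inputs.
- *Visit-by-visit testing will inflate false positives.* Testing change at each of six visits would give a 20-21% chance of at least one false positive per stool outcome, but the protocol does not plan such testing.
- *Blood suffers equally.* Its endpoint has two time points by definition, and the week 8 and 16 draws are mainly for safety.

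**Conclusion.** The point holds for the stool and glucose secondary outcomes. The paired tests that section 10 names fit neither the randomised comparison nor a series of five to seven measurements. The power figures, 0.30-0.59 or about 0.42-0.66 at week 24 against about 0.83-0.91 for the averaged stool contrast, rest on an assumed constant 0.5 SD effect, ρ of 0.3-0.7 and complete data. They also read section 10 generously, because the between-arm test of change used as comparator is not what a paired test does. With a late-building effect there is no gain over an adjusted last-visit comparison. The case for a between-arm model that keeps patients with a missing last sample does not depend on the effect's time course. The primary endpoint, histology at baseline and week 24, is unaffected.

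**What to change.** In section 10, replace the paired tests for continuous secondary outcomes measured more than twice with one linear mixed model per outcome. Include arm, visit, arm-by-visit, the baseline value, the stratification factors of section 8.2 (proton-pump inhibitor use, metformin use, fibrosis score) and within-patient correlation. Report the LFMT-placebo difference with its confidence interval.

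- Stool and glucose: pre-specify the average over post-baseline visits as the main contrast, and also report the last-visit contrast. For glucose, state whether the week-25 recording, which follows the 24-week treatment period, enters the average.
- Blood: keep week 24 as the main contrast, in line with the endpoint definition.

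Reconcile the four and five glucose weeks (sections 8.1.3 and 11.3 against 8.3) and the four and five blood draws (section 8.3 against 11.3), since the model needs a fixed visit list.

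The cost is wording and some analysis time; no new data are needed. The downside is that an average dilutes a late or time-varying effect, which reporting the last-visit contrast makes visible.

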## **11. ETHICAL CONSIDERATIONS**

### **11.1 Regulation statement**

This study will be conducted in accordance with the principles of the Declaration of Helsinki (latest version, October 2013) and in accordance with the regulations in the Medical Research Involving Human Subjects Act (WMO).

### **11.2 Recruitment and consent**

Individuals will be recruited by their treating physician or by advertisements in a newspaper, the patient association or at the outpatient clinics. Nature, aims, methods, anticipated benefits and potential hazards related to the study will be fully explained to the participant prior to applying any study-related procedure by principal investigator, or sub-investigators. Each participant will be informed that his medical records may be reviewed during the course of the Study or afterwards, including review by government agencies. Each participant will be informed that his medical data will be included in a database and may be reviewed during the course of the Study or afterwards, including review by government agencies. However, only authorized personnel will review these data. Each participant will be informed that the investigator will protect any personal information not related to the study, and that individuals associated with the study are bound by the same confidentiality obligations as other health care professionals with regard to subject confidentiality.

Each participant must give written consent according to local rules after an adequate time to consider their decision. Two copies of the consent will be signed before performing any screen evaluations. The consent form will be written in a language that the participant can read and understand. The patient information letter and informed consent form should be attached as a separate document.

The investigator will explain that the participants are completely free to refuse to enter the study or to withdraw from it at any time, without any consequences for their further care and without need for justification. The investigator will complete and sign the informed consent section of the CRF for each participant enrolled.

### **11.3 Benefits and risks assessment, group relatedness**

#### *Benefits*

NAFLD and NASH have an enormous and increasing prevalence: 20-30% of the global population has NAFLD to some extent. NAFLD-related livercirrosis is a growing indication for liver transplantation and the incidence of NASH-related hepatocellular carcinoma is

increasing. The disease progresses slowly and NASH-liver fibrosis is strongly associated with atherosclerotic cardiovascular disease and liver-related and overall mortality. Nevertheless, there is no registered or proven treatment for progressed stages of NAFLD-NASH.

As previously stated, extensive prior research associates the gut microbiome with NAFLD-NASH. Regardless, these studies did not entail a treatment targeting the microbiome to reduce NAFLD-NASH, which would be a big step in the field. Based on available literature on treatment with synbiotics in NAFLD/NASH-patients and our pilot study on FMT in NAFLD/NASH-patients, this trial with adequate sample size endeavours to study if modification of the gut microbiome can attenuate NASH and liver fibrosis.

The benefits the study entails will be discussed in three sections. First, we expect a short term benefit for participants. Our underpowered study in which we administered FMT in NAFLD, showed a trend to reduction of necro-inflammation (i.e. inflammation and ballooning) in histopathological examination. Inflammation and ballooning are the most important predictors of progression of NAFLD-NASH, and subsequent secondary complications. The current study will use LFMT capsules instead of fresh FMT per nasoduodenal tube. This will strongly reduce the burden on participants and will more closely resemble a realistic treatment for NASH. Moreover, recent studies show that LFMT capsules have the same efficacy and show a similar shift of the microbiota composition towards a donor profile, indicating similar engraftment. Half of the individuals will receive the LFMT capsules, and we expect that this already will attenuate NASH. All participants will, in addition, be treated with a complementary synbiotic combination. Multiple small clinical trials already showed a beneficial effect of synbiotics on NAFLD-NASH, without entailing serious side effects. Therefore, we expect a beneficial effect of the synbiotics in both study arms.

Second, participants will be able to benefit from the development of a treatment for NASH. As stated, NASH is a slowly progressing, chronic disease, without an effective treatment. If this study leads to a treatment of NASH, it is likely that participants in the future will receive the investigated treatment. Moreover, participants will assist in further understanding of the pathophysiology of NASH and its relation to the gut microbiome, possibly rendering further leads for the development of a therapy for NASH. Furthermore, the current study and its subsequent insights could not only lead to a treatment, but could also be the basis for preventive measures such as effective and relative easily applicable lifestyle and dietary interventions targeting the gut microbiome.

Last, the current study might benefit health on a population scale. As mentioned, the prevalence of NAFLD and NASH is high and increasing subsequent to the increase of its two main risk factors: obesity and T2DM. Fibrotic-NASH is strongly associated with atherosclerotic cardiovascular events and liver-specific and overall mortality. Considering the

enormous prevalence, this study and its possibility to develop an effective treatment has the potential to benefit the global population on an tremendous scale. Furthermore, in comparison to medicinal alternatives currently investigated in the phase 2 and 3 trials for the treatment of NASH, FMT and synbiotics give a significant reduction of adverse effects.

